### Intervention

The flow of the intervention is outlined in Figure 
1. In the experimental group, the HP will be in charge of the discharge reconciliation and its communication to the CP. To standardize this nonpharmacological intervention over the different hospitals
[26], HPs will receive training in the reconciliation procedure by an experienced clinical pharmacist who is accredited by the French Society of Clinical Pharmacy (SFPC).

**Figure 1 F1:**
[figure not shown]
**REPHVIM study - flow of the intervention.** CP, community pharmacists.

The intervention consists of: 1) identifying the patient’s regular CP, 2) completing a short document including the reason for hospitalization, therapeutic modifications in terms of the home medication, and lab results necessary to understand and/or accept the prescription (estimated glomerular filtration rate, Na and K levels, coagulation results, and so on), 3) controlling the discharge prescription and, if needed, discussing it with the physician and recording it on the SFPC card
[27], 4) explaining the treatment to the patient and the modifications made, 5) phoning the CP to explain the patient’s inclusion in the study, the discharge time, and the modifications in treatment, and 6) sending the CP the prescription sheet via a secure email before patient discharge. The CP will then receive visits from the patient or caregiver as usual. For the control group, pharmaceutical care will be performed as usual, with no reconciliation procedure at discharge and no contact with the CP. REPHVIM study is outlined in Figure 
2.

**Figure 2 F2:**
[figure not shown]
REPHVIM Study - synopsis of the study.

### Blinding

Because of the nature of the assessed intervention, blinding will not be possible for patients or care providers (HPs and CPs). Also, we did not include a blinded outcome assessor because blinding could be easily broken when contacting patients and CPs. Therefore, the present study is fully open, without reliable blinding. The only blinded outcome is a secondary one; the expert committee in charge of assessing the potential medical impact of the DRP will be blinded.

### Sample size calculation

This study is a superiority trial with a binary decision criterion. We hypothesized a DRP rate of 45% in the experimental group as compared to 60% in the control group
[7]. Considering a 90% power and a 5% two-sided alpha level, we would need 235 patients per group with a trial of two parallel, individually randomized groups. We used a sample size calculation software (nQuery Advisor -2005- Version 6.0 Los Angeles, CA. Copyright © 2005 by Janet D. Elashoff). In addition, because the trial is a cluster randomized crossover trial, we assessed both intraclass and interclass correlations
[24,28]. We therefore applied an inflation factor equal to:

(1)$$1\;+\;\left(P\;–1\right)\rho -\mathrm{P\eta}$$

where *P* is the number of patients in a cluster, *ρ* is the intraclass correlation coefficient and *η* is the interclass correlation coefficient. We considered a high value for the intraclass correlation coefficient because the outcome is a process, and because of the incidence of about 50%
[29]. Naturally, *η* is expected to be lower than *ρ*, and we chose the value of *η* to be half that of *ρ* as advised
[24]. We will use a value of 0.2 for *ρ* and 0.1 for *η*.

Because we identified 46 units, we planned to recruit 10.2 patients in each unit for each period. We plan to perform a sensitivity analysis excluding patients without data at day seven after discharge, and so we fixed the number of patients to be recruited in each period to 14. In the end, we expect to recruit 14 patients in each of the 46 units in each period, for 1,176 patients.

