**Methods/Design:**

The study is a cluster randomized crossover trial involving 46 care units (each unit corresponding to a cluster) in 22 French hospitals during two consecutive 14-day periods, randomly assigned as ‘experimental’ or ‘control’ (usual care) periods. We will recruit patients older than 18 years of age and visiting the same CP for at least three months. We will exclude patients with a hospital length of stay of more than 21 days, who do not return home or those in palliative care. During the experimental period, the HP will perform a medications reconciliation that will be communicated to the patient. The HP will inform the patient’s CP about the patient’s drug therapy (modification in home medication, acute drugs prescribed, nonprescription treatments, and/or lab results). The primary outcome will be a composite outcome of any kind of drug misuse during the seven days following discharge assessed at day seven (±2) post-discharge by a pharmacist in charge of the study who will contact both patients and CPs by phone. The secondary outcome will be unplanned hospitalizations assessed by phone contact at day 35 (±5) after discharge. We plan to recruit 1,176 patients.

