### Setting and participants

In total, 22 French HPs working in hospitals all over the French country have agreed to participate. Each HP selected two units (one surgical, one medical) in their hospital. Units for which a pharmaceutical reconciliation procedure at admission or discharge was already in place were not eligible. The medical heads of the units also agreed to participate. We will exclude patients with a length of stay of more than 21 days (as there can be too many therapeutic modifications during the stay), who do not return home, who are in palliative care and/or near the end of life, and who are not able to understand the topic.

CPs working in the area around the hospital will participate by the inclusion of their patients in the study. They will be informed of the study in three ways: a professional journal supported by the pharmacist unions, a professional journal supported by the national council of the order of pharmacists, and a letter sent by the study scientific committee distributed by wholesale drug distributors.

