## Trial status

At this time, 44 units have been recruited since 21 January 2014 and 340 patients have been included.

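### The stated sample size does not match the stated design: 14 patients × 46 units × 2 periods is 1,288, not 1,176, and 10.2 per unit-period does not follow from 46 units

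*Protocol article*

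**What the plan says.** The sample size section assumes 60% of control patients and 45% of experimental patients with a drug-related problem, 90% power and a two-sided 5% level. It obtains 235 per group for an individually randomized parallel trial. It then multiplies by 1 + (P − 1)ρ − Pη, with ρ = 0.2 and η = 0.1, where P "is the number of patients in a cluster".

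The size per unit follows: "Because we identified 46 units, we planned to recruit 10.2 patients in each unit for each period". This is raised to 14 to allow for patients without day-seven data, and the section closes with "In the end, we expect to recruit 14 patients in each of the 46 units in each period, for 1,176 patients".

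The abstract gives the same unit count, "46 care units (each unit corresponding to a cluster) in 22 French hospitals", over two periods, and the same total of 1,176. Setting and participants reports 22 hospital pharmacists and says "Each HP selected two units (one surgical, one medical) in their hospital". Trial status reports that "44 units have been recruited since 21 January 2014".

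**The concern.** Units, patients per unit-period and total are three figures of which any two fix the third, and here they do not agree. The 10.2 is presented as a consequence of having 46 units, so it should be recoverable from the protocol's own formula, but it is not. If the calculation was made for a different number of clusters from the one stated, a reader cannot reproduce the sample size. It is then unclear which overall total is intended and how much loss of day-seven data the 14 allows for. Recruitment was already under way at publication, with 340 patients included.

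**Working it through.** **Inputs, all from Sample size calculation unless noted.** Rates 0.60 and 0.45; power 90%; two-sided α 5%; base n 235 per group; ρ = 0.2; η = 0.1; 46 units; 10.2 needed and 14 recruited per unit-period; total 1,176. Two periods per unit (Design).

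**Step 1: the 235.** The log-odds-ratio formula gives (1.960 + 1.282)² × (1/0.24 + 1/0.2475) / 0.606² = 234.7, so 235 reproduces. Other common formulas give 228 (unpooled), 231 (pooled) and 244 (continuity-corrected). The base figure is sound.

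**Step 2: patients needed per unit-period.** Each of K units contributes P patients to each arm, so the requirement is

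K × P = 235 × [1 + (P − 1)(0.2) − P(0.1)] = 235 × (0.8 + 0.1P),

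which gives P = 188 / (K − 23.5).

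**Step 3: total recruited** = 14 × K × 2.

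| Units K | P needed | Total at 14 per unit-period | Loss that 14 allows, 1 − P/14 |
|---|---|---|---|
| 42 | 188/18.5 = 10.16 | 1,176 | 27% |
| 44 | 188/20.5 = 9.17 | 1,232 | 34% |
| 46 | 188/22.5 = 8.36 | 1,288 | 40% |

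Only the 42-unit row gives both stated figures. Working back, 1,176 / (14 × 2) = 42 exactly, whereas 1,176 / (46 × 2) = 12.8.

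**Step 4: can another input rescue 46 units?** With a base n of 228 to 244, P for 46 units runs from 7.8 to 9.0 and never reaches 10.2. Obtaining 10.2 with 46 units would need η of about 0.083 instead of the stated 0.1, and that would leave the total of 1,176 unexplained.

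**Step 5: unit count.** 22 pharmacists × 2 units = 44, against 46 in the abstract and the sample size section.

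**Step 6: effect on power.** The effective n per group is K × P / (0.8 + 0.1P). The implied loss is 1 − 10.2/14 = 27%.

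- 1,176 over 44 units: 13.4 recruited and 9.7 evaluable per unit-period; effective n 241.5.
- 1,176 over 46 units: 12.8 recruited and 9.3 evaluable; effective n 247.4.

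Both exceed 235. Scaled from 235 at 90%, power is 90.8% and 91.4%. With the pooled two-proportion formula it is 91.3% and 91.9%. If 10.2 evaluable per unit-period is reached, power is 91.3% to 91.8% with 44 units and 92.4% to 92.9% with 46.

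**The case against.** The case on the other side is about consequences, since the multiplication itself cannot be defended. Several stronger readings are tempting, and the protocol does not support them.

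- *The trial is underpowered.* A reader might infer this from a calculation made for the wrong number of clusters. The opposite holds: 10.2 is more than 44 or 46 units need, so the error is conservative under the stated assumptions.
- *The figures were computed for 42 units.* The protocol nowhere mentions 42. Two figures fit that count, and neither fits 44 or 46, so the inference is strong. It is still an inference; what is established is the mismatch with 46.
- *The recruitment target is undefined.* Each unit takes part for two fixed 14-day periods with 14 patients expected in each, which can be followed whatever the total. Read as minimums, 14 per unit-period in 44 or 46 units also exceeds 1,176. Only the overall total is ambiguous. The protocol does not say what sites or the sponsor were told.
- *Trial status contradicts 46 units.* Its 44 is a count to date and is compatible with a plan of 46. The real conflict is with the two units for each of 22 pharmacists.
- *P covers both periods.* Since a cluster is a unit, a reader might put P = 20.4 into the formula and get a factor of 2.84 instead of 1.82. But the protocol applies 10.2 to each unit in each period, so its intended use of P is recoverable. Only the definition is loose.

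These objections limit the consequences. They leave the wrong total, the 10.2 that does not follow from 46 units, and the 44-versus-46 conflict in place.

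**Conclusion.** The sample size statement is internally inconsistent and should be corrected. The total is 112 patients short of what 14 per unit-period in 46 units yields, or 56 short with 44 units (1,232 − 1,176). The requirement of 10.2 per unit-period should read 8.4 for 46 units or 9.2 for 44. The allowance for missing day-seven data therefore depends on the count adopted: 27% as written, 34% with 44 units, 40% with 46.

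This is an error in a stated design quantity, not a threat to the trial's power, which stays at about 91% or higher in every 44- or 46-unit scenario examined. That conclusion rests on the protocol's event rates, ρ = 0.2, η = 0.1, equal numbers per unit-period and losses of no more than about 27%.

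**What to change.** 1. State one planned number of units in the abstract, Setting and participants, and Sample size calculation. If it is 46, explain how 22 pharmacists selecting two units each gives 46.
2. Restate the evaluable patients needed per unit-period: 8.4 for 46 units or 9.2 for 44.
3. Make the recruitment figures agree in one of two ways. Either keep 14 per unit-period and restate the total as 1,288 (46 units) or 1,232 (44 units), or keep 1,176 and restate the average per unit-period as about 12.8 (46 units) or 13.4 (44 units).
4. State the loss of day-seven data that the chosen figure allows for.
5. Define P as patients per unit per period.

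The cost is a few corrected sentences. No extra patients are needed if 1,176 is kept, and neither the design nor the analysis changes.

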### Statistical analysis

The primary analysis will be conducted within the framework of a hierarchical model, inspired by the work of Turner *et al*.
[30]. Under this model, two levels of correlation are considered: intra-cluster correlation and cross-correlation period. Secondary outcomes will also be analyzed with hierarchical models. Subgroup analyzes will consider patient characteristics (age and pathology), drugs classes, nature of the unit (surgery or medical), number of home treatments, day of discharge (weekday or weekend), whether it is an expensive drug (more than 150€ per unit) is prescribed, and whether some medications require temperature control.

### Dissemination

The scientific committee will be in charge of the publications to report the results of the present study. Reports will follow the CONSORT statement and its extensions (for both cluster randomized trials and nonpharmacological interventions), as well as the TIDER checklist.

## Discussion

This study will investigate the effect of HP reconciling medications with the patient at discharge and communicating with the patient’s CP on preventing DRPs. The subgroups study will evaluate the patients for which the process would be efficient. The French Society of Clinical Pharmacy is expected to write recommendations and promote communication between HPs and CPs. We expect a decrease in DRPs from 60 to 45%.

The success of the study depends on the ability of the HP to enroll patients in the study. The units have been chosen for their possibility of having more than one discharge a day. Most are surgery units (orthopedic, urology, or general surgery) and medical units (nephrology, gastroenterology, internal medicine, and so on) with a large number of beds (more than 20) and a mean length of stay from 5 to 11 days. Patients in the intervention group need to spend only a few minutes of discussion with the HP. This intervention will need to be performed as soon as possible once discharge is planned. Indeed, at discharge, patients are usually stressed with transport and other administrative issues, so they may be less receptive to discuss their treatment.

To optimize and standardize the intervention assessed, the scientific committee has established a training program for HPs. Also, quality documents have been written to ensure performance of the same intervention. Outcome assessments will be performed centrally by two pharmacists (pharmacists in charge of the study) specially recruited for the study, which will favor homogeneity in the phone interviews.

## Trial status

At this time, 44 units have been recruited since 21 January 2014 and 340 patients have been included.

## Abbreviations

CP: Community pharmacist; CH: Hospital (Centre Hospitalier); CHU: University hospital (Centre Hospitalier Universitaire) DRP, Drug-related problem; eDFG: Estimated Glomerular Filtration Rate; ENEIS: National Study on Iatrogenic Event Avoidable; GP: General practitioner; HP: Hospital pharmacist; ID: Intentional discrepancy; NID: Non intentional discrepancy; PCS: Pharmacist in charge of the study; PREPS: Research program on the performance of care system; SFPC: French society of clinical pharmacy.
